### Blinding

In this study, the participants, the outcome assessors, and the data managers, including the statistician, will be blinded to the group allocation. The acupuncture practitioner will not be blinded because of the characteristics of the Park sham device. The investigators will not give any clues to the participants regarding group allocation, nor will the participants from one group meet those from the other group. To evaluate the success of blinding, a blinding index will be assessed after the participants’ final treatment. Blinding will be maintained until the study is finished. However, if a serious adverse event (AE) occurs, blinding will be lifted, and investigators will notify the participant involved of his/her group allocation in accordance with the standard operating procedures (SOPs).

### Intervention

In Table 1, we have provided detailed information regarding the EA treatment to be used; the treatment will be based on the revised Standards for Reporting Interventions in Clinical Trials of Acupuncture (STRICTA) [20]. Furthermore, we have tried to reconstruct a real clinical environment in the study design, using partially individualized EA treatments based on both meridian theory and the consensus of Korean medicine gastroenterologists. Individualized treatment will be carried out according to the participant’s pattern identification. At the first visit, the participant will respond to a GERD pattern identification tool [21], and the pattern of the participant will be identified as one of following four types: “liver qi invading the stomach,” “spleen-stomach weakness,” “spleen-stomach dampness-heat,” and “stomach yin deficiency.” The participants’ identified types will not change for the duration of the study.

**Table 1 Tab1:** Acupuncture treatment details based on the STRICTA 2010 checklist

Item	Detail
1. Acupuncture rationale	1a) Style of acupuncture - EA based on traditional meridian theory.
	1b) Reasoning for treatment provided, based on historical context, literature sources, and/or consensus methods, with references where appropriate - Partially individualized manual EA treatments based on the traditional meridian theory, literature review, consensus by the experts in GERD and acupuncture, and clinical experience of Korean medicine gastroenterologist.
	1c) Extent to which treatment was varied - Partially individualized EA treatment, i.e., fixed points plus optional points according to pattern identification of the participant.
2. Details of needling	2a) Number of needle insertions per subject per session (mean and range where relevant) - From 18 to 20.
	2b) Names (or location if no standard name) of points used (uni/bilateral) - Eighteen fixed points: ST36, a point 0.5 cun below ST36, PC6, LI4, LR3, SP4, SP9, GB34 (bilateral), CV10, and CV13 (unilateral). - Optional points according to individual pattern identification (1) “Liver qi invading the stomach” type: SP11, LR2 (Rt. side) (2) “Spleen-stomach weakness” type: CV12 (one point), ST41 (Rt. side) (3) “Spleen-stomach dampness-heat” type: LR13, SP3 (Rt. side) (4) “Stomach yin deficiency” type: CV12 (one point), ST44 (Rt. side)
	2c) Depth of insertion, based on a specified unit of measurement, or on a particular tissue level - From 5 to 30 mm.
	2d) Response sought (e.g., *de qi* or muscle twitch response) - none
	2e) Needle stimulation (e.g., manual, electrical) - Electrical stimulation: 2/6 Hz mixed (ITO ES-160, Japan) - Acupoints with electrical stimulation: ST36, a point 0.5 cun below ST36, PC6, LI4 (bilateral), CV10, and CV13 (unilateral).
	2f) Needle retention time - 20 minutes.
	2g) Needle type (diameter, length, and manufacturer or material) - Park sham device with real and sham needle, i.e., sterilized stainless steel needle (0.25 x 40 mm, Dongbang Acupuncture Inc., Bundang, Sungnam, Korea).
3. Treatment regimen	3a) Number of treatment sessions - Twelve treatment sessions in both EA and sham EA groups.
	3b) Frequency and duration of treatment sessions - Twice weekly for 6 weeks, 20 minutes for each session.
4. Other components of treatment	4a) Details of other interventions administered to the acupuncture group (e.g., moxibustion, cupping, herbs, exercises, lifestyle advice) - Except for lifestyle modification and rescue medicine, other interventions during the study period will not be allowed.
	4b) Setting and context of treatment, including instructions to practitioners, and information and explanations to patients - Korean Medicine Clinical Trial Center in University hospitals - Participants will be informed about acupuncture treatment in the study as follows: “In this study, classic and nonclassic acupuncture treatment for GERD will be used based on traditional Korean medicine textbook and GERD- related literature.”
5. Practitioner background	5) Description of participating acupuncturists (qualification or professional affiliation, years in acupuncture practice, other relevant experience) - Two Korean Medicine Doctors who have licenses and at least 5 years of experience in gastrointestinal disorders. They went through training and simulation to ensure that they are able to provide identical EA treatment on the ground of predefined protocol and standard operating procedure.
6. Control or comparator interventions	6a) Rationale for the control or comparator in the context of the research question, with sources that justify this choice - A sham EA group using Park sham device with sham needle will be adopted.
	6b) Precise description of the control or comparator. If sham acupuncture or any other type of acupuncture-like control is used, provide details as for Items 1 to 3 above. - Participants in the sham EA group will receive acupuncture treatment after randomization twice weekly for 6 weeks. - Sham EA group: nonpenetrating, nonacupoint, nonelectric current (1) Device: Park sham device with sham needle (2) Acupoint: Eighteen acupoints. Each acupoint is 2 cm apart from the acupoints of EA group to the medial side. (The optional points in accordance with pattern identification will not be included) (3) Duration of treatment sessions: 20 minutes

*STRICTA* STandards for Reporting Interventions in Clinical Trials of Acupuncture; *EA* elctroacupuncture, *GERD*, gastroesophageal reflux disease, *ST* stomach, *PC* pericardium, *LI* large intestine, *LR* liver, *SP* spleen, *GB* gallbladder, *CV* conception vessel

The treatment will consist of 12 sessions across 6 weeks (two sessions each week); it will be performed by KMDs with more than 5 years of clinical experience in acupuncture, who will go through training and simulation to ensure identical acupuncture treatment in accordance with the SOPs. The minimum interval between treatment sessions will be 2 days. Lifestyle will be modified in both groups.

#### EA group

The number of inserted needles per participant in one session will range from 18 to 20. The basic points and optional points used will be included in the acupuncture treatment regimen. All participants will undergo acupuncture treatment at 18 fixed points. The details of the acupoints are shown in Table 1. Of these points, electrical stimulation will only be applied to ST36, a point 0.5 cm below ST36, PC6, LI4 (bilateral), CV10, and CV13 (unilateral). In addition, optional points will be selected on the basis of the participant’s pattern identification; the details are shown in Table 1.

We will use a Park sham device (Acuprime, Exeter, UK) with real penetrating needles [22]; the inserted needle of this device is a sterilized stainless steel needle (DongBang Acupucture Inc., Bundang, Sungnam, Republic of Korea) 40 mm in length and 0.25 mm in diameter. The needles will be inserted to a depth of between 5 mm and 30 mm, and they will remain in place for 20 minutes. In the case of EA points, the needles will be stimulated using a mixed electric current at a frequency of 2/6 Hz; to this end, the “fast plus slow” mode of the ES-160 (ITO Co., Ltd., Tokyo, Japan) will be used. The stimulation intensity will be adjusted depending on the degree of the participant’s tolerance.

#### Sham EA group

Participants in the sham EA group will be treated using 18 fixed acupoints. However, acupoints based on individual pattern identification will not be used. We will use a Park sham device with sham (blunted) needles [22] that do not penetrate the skin; this device has been described in previous studies [23–25]. At the EA points, the same accessories of the EA equipment will be assembled, and there will be a timer sound and a blinking light; however, no electrical current will be applied.

#### Lifestyle modification

In accordance with the clinical practice guidelines for GERD [26], as well as the SOP, lifestyle modification will be taught to participants by the KMD at every visit. Lifestyle modification will comprise (1) avoidance of foods that worsen GERD symptoms (e.g., coffee, alcohol, chocolate, fat, etc.), (2) avoidance of foods that cause heartburn (e.g., spicy food, fruit, carbonated drinks, etc.), (3) changes to lifestyle that decrease the exposure of the lower esophagus to gastric acid (e.g., weight loss, cessation of smoking and of drinking alcohol, raising the upper part of the bed, going to bed 2–3 hours after a meal) [27].

#### Distribution of rescue medicine

With regard to ethics, we will distribute the rescue medicine, named Norumo Dual Action Suspension (Il-Yang Pharmaceutical Co., Ltd., Gangnam, Seoul, Republic of Korea), to all participants. If participants experience intolerable GERD symptoms between visits, they will be permitted to take one pack. The ingredients of the medicine are sodium alginate, sodium bicarbonate, and calcium carbonate. The number of rescue medicines administered will be evaluated at each visit. If the number between visits is more than three, then the primary outcome, adequate relief (AR), will be classified as “no relief,” regardless of the participant’s answer.

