### Withdrawal criteria

Participants will be withdrawn from the study if they (1) miss a scheduled EA treatment three times in a row or (2) take forbidden medication, herbal medicine, or undergo surgery related to GERD during the study period.

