#### Primary outcome

We set the “proportion of responders” (PR) [28, 29] as the primary outcome. PR is the proportion of participants who respond “yes” to more than half of the AR-related questions during the treatment period [30]. An assessor will ask the participants the following question at each visit during the treatment period (twice a week for 6 weeks): “Have you had adequate relief of the pain or discomfort caused to you by GERD since the last visit?” We will define AR as ‘improvement of GERD symptoms by ≥ 20 % since the last visit.

If participants report AR at more than half of all treatment sessions, they will be defined as responders, and we will compare the proportion of responders between the EA and sham EA groups.

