### Statistical analysis

An independent statistician blinded to group allocation will carry out the statistical analysis using SPSS™ 18.0 (SPSS Inc., Chicago, Illinois, USA). All final data will be securely stored, and only the statistician will have access. We will perform both intention-to-treat (ITT) and per protocol (PP) analysis, with all analyses being based on the ITT principle. Any participant who receives EA more than nine times during the study period will be eligible for PP analysis.

For ITT analysis of secondary outcomes, we will use the “last observation carried forward” rule. In the case of the primary outcome, however, missing values will not be replaced, because of the characteristics of adequate relief (AR). We will only count actual responses regarding AR. When AR occurs in more than 50 % of the treatment sessions in which a study subject participated, the participant will be classified as a responder. All data will be shown as the mean ± standard deviation (SD) or as numbers and percentages. The statistical significance level will be set at 0.05 (two-sided), with 95 % confidence intervals (CI). The analysis for safety will also follow the principles of ITT.

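### The rescue override uses a fixed pack count per inter-visit interval, so missed sessions make 'no relief' more likely at unchanged rescue use

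*Protocol article*

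**What the plan says.** All references are to the protocol article.

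- *Distribution of rescue medicine*: "The number of rescue medicines administered will be evaluated at each visit". Then: "If the number between visits is more than three, then the primary outcome, adequate relief (AR), will be classified as" no relief, regardless of the answer given.
- *Intervention*: 12 sessions are planned, two a week for 6 weeks. "The minimum interval between treatment sessions will be 2 days". No maximum is given.
- *Withdrawal criteria*: a participant leaves the study on missing treatment ("miss a scheduled EA treatment three times in a row"), so one or two consecutive misses are tolerated.
- *Primary outcome*: the question at each visit is "Have you had adequate relief of the pain or discomfort caused to you by GERD since the last visit". Responder status is built from these answers: "If participants report AR at more than half of all treatment sessions, they will be defined as responders".
- *Statistical analysis*: missing answers are not replaced, and the denominator is attended sessions: "When AR occurs in more than 50 % of the treatment sessions in which a study subject participated". More than nine sessions qualifies a participant for the per-protocol analysis.

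**The concern.** A count accumulates with time. If a session is missed, the next answer is tested against the packs taken over two or three planned intervals, but the limit stays at three. The missed session itself drops out of the denominator, so absence is not directly scored as failure. It is partly scored indirectly, because the next attended visit is more likely to be overridden at the same daily rescue use.

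At stake is misclassification of the primary endpoint that depends on attendance rather than symptoms. With 30 per arm, one misclassified participant moves an arm's responder proportion by 1/30 = 3.3 percentage points. If attendance differed between arms, the comparison would be biased.

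**Working it through.** The plan gives no figure for rescue use, so there is none to reproduce. Pack rates and the participant's own answers below are assumptions.

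**Inputs from the protocol.** Override at 4 or more packs in an interval; 12 answers (Table 2, V2 to V13); mean planned interval 7/2 = 3.5 days, taken as alternating 3 and 4 days; responder if relief is recorded at more than half of attended sessions.

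**Step 1: interval lengths.** On a 3/4-day schedule one missed session joins two intervals: 3 + 4 = 7 days. Two in a row give 10 or 11 days.

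**Step 2: daily use that reaches four packs.** 4/3 = 1.33; 4/4 = 1.0; 4/7 = 0.57; 4/11 = 0.36 packs a day.

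**Step 3: chance that one answer escapes the override.** For Poisson use with mean m = rate × days, P(3 or fewer) = e^(−m)(1 + m + m²/2 + m³/6).

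| Rate per day | 3 days | 4 days | 7 days |
|---|---|---|---|
| 0.6 | 0.891 | 0.779 | 0.395 |
| 0.8 | 0.779 | 0.602 | 0.191 |

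For example, 0.8 × 7 = 5.6 and e^(−5.6)(1 + 5.6 + 15.68 + 29.27) = 0.191.

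**Step 4: responder probability, participant always answers yes.** Full attendance: six 3-day and six 4-day intervals, at least 7 of 12 needed. Two separate misses: four 3-day, four 4-day and two 7-day intervals, at least 6 of 10 needed. Summing the binomial terms:

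| Rate per day | 12 of 12 attended | 10 of 12 attended |
|---|---|---|
| 0.6 | 0.993 | 0.939 |
| 0.8 | 0.871 | 0.624 |

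**Step 5: how much is due to the longer window?** Part of the fall comes from needing 6 of 10 rather than 7 of 12. Ten ordinary intervals (five of 3 days, five of 4) give 0.986 at 0.6 a day and 0.838 at 0.8. The remaining falls, 0.986 to 0.939 and 0.838 to 0.624, come from the longer window.

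**Step 6: other attendance patterns, same model.**
- One miss (11 attended, at least 6 needed): 0.991 at 0.6 a day and 0.859 at 0.8, so little change.
- Two misses in a row (one 10- or 11-day interval): 0.956 to 0.965 at 0.6 a day and 0.695 to 0.738 at 0.8.
- Every second visit missed (six 7-day intervals): 0.173 at 0.6 a day and 0.014 at 0.8.

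**Step 7: visit spacing with full attendance.** The 3/4-day against the 2/5-day schedule gives 0.962 and 0.962 at 0.7 a day, 0.871 and 0.884 at 0.8, and 0.499 and 0.567 at 1.0. If each answer is yes with probability 0.8, the figures at 0.7 a day are 0.698 and 0.655.

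**The case against.** The strongest defence is that the count uses the same recall window as the relief question, since both run from the last visit, and that twice-weekly sessions keep most windows short. That is a reasonable design for visits attended as planned. It does not cover missed visits: the relief question remains a yes/no judgement over a longer window, whereas a count grows with days.

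It is also fair that the effect is conditional. The override changes one visit's answer, and status changes only if such visits, with the participant's own negative answers, leave relief at half or fewer of attended sessions. One miss barely matters, and the largest effects need half the visits missed. The packs are for intolerable symptoms, and nothing in the protocol shows use near 0.6 to 0.8 a day. Nor does it give reason to expect attendance to differ by arm in a participant-blinded trial.

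A reader might infer that visit spacing alone decides who is a responder. Examples can be built: five packs a week on days 1, 3, 4, 5 and 7 give 12 of 12 on a 3/4-day schedule but 6 of 12 on one 2/5-day schedule. They depend on exact timing. Under random use the two schedules differ by at most about 7 points, in either direction, because the short interval offsets the long one.

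**Conclusion.** The point holds for missed sessions. A fixed count per inter-visit interval, with no maximum interval and up to two consecutive misses tolerated, makes the override more likely at unchanged rescue use and works against the attended-sessions denominator. Under the stated assumptions, two separate misses lower the responder probability by about 5 points at 0.6 packs a day (0.993 to 0.939) and 25 points at 0.8 (0.871 to 0.624). Someone attending 10 of 12 sessions still has more than nine, so this pattern also reaches the per-protocol set. Bias between arms is possible only if attendance differs by arm, which the documents neither state nor suggest.

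A reader might also infer that one breach makes the participant a non-responder, because the rescue section calls adequate relief the primary outcome. The *Primary outcome* section does not support this: the primary outcome there is the proportion of responders, built from answers at each visit. The two sections still need to be reconciled, since on the literal reading a single long interval would decide the endpoint.

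**What to change.** Change the endpoint definition only, not what participants may take.

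1. Tie the count to the planned inter-visit interval. Where an interval is lengthened by a missed session, do not judge it on the same raw count; for example, scale the count to the number of planned intervals spanned. The sponsor's threshold for visits attended as planned stays as it is. As a check on the principle, allowing three per planned interval (six over a 7-day interval spanning two) in the model above gives 0.829 at 0.8 a day with 10 of 12 attended, close to the 0.838 for ten ordinary intervals, against 0.624 now.
2. State that the override applies to that visit's relief answer only, and reconcile *Distribution of rescue medicine* with *Primary outcome* accordingly.

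A plain per-day rate is not equivalent. Three packs per 3.5 days is 0.857 a day, so three packs in 3 days would trigger the override, which the present rule does not do. For full attenders at 0.8 a day the responder probability would fall from 0.871 to 0.628.

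The cost is about one added sentence and slightly more derivation work from visit dates and pack counts already collected. No extra visits or data are needed.

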### Withdrawal criteria

Participants will be withdrawn from the study if they (1) miss a scheduled EA treatment three times in a row or (2) take forbidden medication, herbal medicine, or undergo surgery related to GERD during the study period.

### Drugs forbidden by the study protocol

The following classes of drugs, all of which are used to treat symptoms of GERD, will not be allowed: PPIs, histamine receptor antagonists, prokinetics, mucosal protective drugs, antacids, anti-depressants, antianxiety drugs, lower esophageal sphincter agents, and herbal medicine.

### Outcome measurement

An independent assessor will give the participants a set of outcome measures; a schedule of these measures is summarized in Table 2.

**Table 2 Tab2:** Study schedule for data collection

Measures	V1	V2	V3	V4	V5	V6	V7	V8	V9	V10	V11	V12	V13
Sociodemographic data	✔												
GERD pattern identification tool	✔												✔
Collection and distribution of diary	✔		✔		✔		✔		✔		✔		✔
Assessment of beliefs in the acupuncture effectiveness	✔												
Adequate relief (AR)		✔	✔	✔	✔	✔	✔	✔	✔	✔	✔	✔	✔
Nepean Dyspepsia Index - Korean (NDI-K)	✔					✔							✔
Numeric rating scale (NRS) for GERD	✔					✔							✔
Korean Gastrointestinal Symptom rating scale (KGSRS)	✔					✔							✔
EuroQol-5 Dimension (EQ-5D)	✔					✔							✔
Perceived Stress Scale-Korean (PSS)	✔					✔							✔
Gut hormones (gastrin and motilin)	✔												✔
Blood collection for cytokine analysis	✔												✔
Qi stagnation and spleen Qi deficiency questionnaire	✔												✔
PGIC GERD symptom						✔							✔
Blinding Index (BI) and cCredibility test													✔
Adverse events investigation		✔	✔	✔	✔	✔	✔	✔	✔	✔	✔	✔	✔
Assessment of concomitant therapy and lifestyle modification	✔	✔	✔	✔	✔	✔	✔	✔	✔	✔	✔	✔	✔
Evaluation of rescue medicines		✔	✔	✔	✔	✔	✔	✔	✔	✔	✔	✔	✔

#### Primary outcome

We set the “proportion of responders” (PR) [28, 29] as the primary outcome. PR is the proportion of participants who respond “yes” to more than half of the AR-related questions during the treatment period [30]. An assessor will ask the participants the following question at each visit during the treatment period (twice a week for 6 weeks): “Have you had adequate relief of the pain or discomfort caused to you by GERD since the last visit?” We will define AR as ‘improvement of GERD symptoms by ≥ 20 % since the last visit.

If participants report AR at more than half of all treatment sessions, they will be defined as responders, and we will compare the proportion of responders between the EA and sham EA groups.

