### Sample size calculation

The required sample size was calculated on the basis of the difference in PR between the EA and sham EA groups. On the basis of previous research [55], we assumed the PR would be 92.8 % in the treatment group and 57.1 % in the control group. With a 5 % false positive error (*α* = 0.05, two-sided) and 80 % power (*ß* = 0.2) the required sample size in each group was *n* = 21.9. Assuming a 25 % of dropout rate, the real-world sample size will be *n* = 30 in each group, for a total of 60 participants.

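### Adequate relief is defined as a 20% improvement since the previous visit, so read literally a patient who improves early and stays well is a non-responder, and the definition conflicts with the question asked

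*Protocol article*

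**What the plan says.** In the protocol article, Outcome measurement, Primary outcome, an assessor asks each participant twice a week for six weeks: "Have you had adequate relief of the pain or discomfort caused to you by GERD since the last visit". The next sentence defines AR as "improvement of GERD symptoms by ≥ 20 % since the last visit". The responder rule follows: "If participants report AR at more than half of all treatment sessions, they will be defined as responders". Table 2 schedules AR at V2 to V13, which is 12 assessments.

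Two other sections touch the rule. The Statistical analysis section counts over sessions attended: "When AR occurs in more than 50 % of the treatment sessions in which a study subject participated, the participant will be classified as a responder". The section on rescue medicine sets AR to no relief above a stated count, "regardless of the participant’s answer". Neither ties AR to baseline, and nothing in the article says that maintained relief counts as a yes.

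The Sample size calculation section builds on this endpoint: "The required sample size was calculated on the basis of the difference in PR between the EA and sham EA groups", and "we assumed the PR would be 92.8 % in the treatment group and 57.1 % in the control group".

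**The concern.** The definition moves its reference point at every visit. After a patient has improved, the improved state becomes the new reference, and only a further 20% fall within three to four days earns another yes. A patient who gets better in the first week and stays better has nothing further to report, and each later visit is a no.

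The stated hypothesis is that electroacupuncture eases GERD symptoms more than sham. Early and lasting relief is the result that hypothesis hopes for, and the written rule scores it as failure on the only primary endpoint.

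The question put to the patient does not clearly carry the same meaning. On its own it reads as a recall window: was there adequate relief during the days since the last visit? On that reading, maintained relief is a yes. If some patients or assessors follow the question and others follow the definition, the endpoint mixes two rules.

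**Working it through.** **Inputs from the article.** Threshold 20%, reference the previous visit; 12 AR assessments (V2 to V13); responder if AR at more than half, so at least 7 of 12 with full attendance; planning rates 0.928 and 0.571, two-sided alpha 0.05, power 80%, dropout 25%.

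**The plan's own figure.** Pooled two-proportion formula, with p̄ = (0.928 + 0.571)/2 = 0.7495:

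n = [1.96·√(2·0.7495·0.2505) + 0.8416·√(0.928·0.072 + 0.571·0.429)]² / (0.928 − 0.571)²

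= (1.2010 + 0.4699)² / 0.12745 = 21.9 per group.

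This matches the article. Rounded up to 22, then 22/0.75 = 29.3, so 30 per group. The arithmetic is not in dispute.

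**What a responder without rebound needs.** Seven falls of at least 20% multiply to 0.8^7 = 0.210. Symptoms must end at or below 21% of the start, a fall of at least 79%, spread over seven separate visits.

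**Counting the rule on example paths.** The paths are assumptions: a baseline of 10 followed by 12 assessments.

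| Path | Yes, since last visit | Yes, against baseline |
|---|---|---|
| 10 to 4 at the first assessment, then held | 1/12, non-responder | 12/12, responder |
| 10, 7, 4, 2, then held | 3/12, non-responder | 12/12, responder |
| 10% fall at every visit, ending at 2.8 | 0/12, non-responder | 10/12, responder |

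These counts need no noise model and establish the point.

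**With visit-to-visit noise.** Illustrative model: 0-10 score starting at 6, independent normal noise at each visit with the SD shown. Percentage classed as responders, written rule versus the same 20% threshold set against the V1 value:

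| True course | SD 0.5 | SD 1 | SD 1.5 |
|---|---|---|---|
| Early 60% improvement, held | 0.2 vs 100 | 6 vs 99.6 | 12 vs 96 |
| Straight-line fall to 60% improvement | <0.1 vs 89 | 1 vs 74 | 4 vs 66 |

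A separate model with lognormal noise (log-SD 0.2 to 0.5) gives the same picture: a sustained 50% drop passes the written rule in 0.1% to 6% of patients, against 98% to 79% when measured from baseline.

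**Can it be repaired at analysis?** Table 2 schedules the 11-point rating only at V1, V6 and V13. The other symptom scales (NDI-K and KGSRS) follow the same three visits. A diary is collected every second visit, but the article does not say that it records symptom severity. On what is shown, the 12 AR answers cannot be re-derived later under a different reference point.

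**The case against.** The strongest reply is that AR is a spoken yes/no answer and not a computed percentage. No score is taken at each visit, so patients will answer the question as they hear it, and many will hear it as a recall window. If they do, sustained relief is counted correctly and the contrasts above do not arise. This stands in part: those figures apply only if answers follow the 20% sentence. It does not remove the problem, because that sentence is an explicit definition placed next to the question, and the two can give opposite answers for the same patient.

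Three stronger readings are tempting, and the documents do not support them.

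- *That patients who merely fluctuate will often be counted as responders.* Such a path can be built: 15, 12, 9.6 repeated from a baseline of 10 scores 8/12 under the written rule and 0/12 against baseline. But the simpler cycle 8, 6.4, 10 scores 8/12 under both rules, and plain alternation 10-8-10-8 scores 6/12 and fails. In the illustrative model at SD 1, patients with no true change pass the written rule in well under 0.01% of cases, against about 7% with a V1 reference. At SD 2 the figures are 0.7% and 21%. Chance passes are rarer under the written rule.
- *That the planning rates are impossible and the 80% power void.* Rates of 92.8% and 57.1% are hard to square with repeated fresh 20% falls, but not with the recall-window reading. The responder definition behind them lies in a cited source that is not available here.
- *That the primary endpoint does not measure symptom relief at all.* It measures it badly if read literally. Change from baseline is also captured by the secondary scales, though these do not repair the primary endpoint.

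**Conclusion.** The point holds for sustained relief. As written, the AR definition turns early and lasting improvement into non-response: 1/12 for an immediate 60% fall that is held, and 3/12 for an 80% improvement reached in three steps, where at least 7/12 is required. It also conflicts with the natural reading of the question beside it. This is a stated rule of the sole primary endpoint, so it is not a detail that an article would leave to another document.

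The counts assume full attendance and answers given strictly by the 20% sentence. The simulated percentages rest also on assumed courses and noise levels and are illustrative only. How many patients would be misclassified cannot be estimated from the article, because it depends on which of the two readings they follow.

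The sample size of 21.9, then 30, per group reproduces. What remains open is whether the planning rates refer to the same responder definition; the article does not show that they do.

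**What to change.** Define AR as adequate relief during the interval since the last visit, compared with the state before treatment, with the 20% threshold set against V1. Use the last visit only to mark the recall period. Reword the question to match, for example: over the days since your last visit, have you had adequate relief of your GERD pain or discomfort compared with before treatment began? Keep the more-than-half rule. State in the sample size section that the rates of 92.8% and 57.1% use this definition, or revisit them if they do not.

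The cost is new wording in the case report form and assessor script and an amendment to the ethics board, with no extra patients, visits or procedures. It has to be done before AR answers are collected. One statistical downside should be accepted knowingly: with a single V1 value as the reference for all 12 answers, more patients with no true change pass by chance, about 7% at SD 1 in the illustrative model and 21% at SD 2.
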